## Abstract

**Background::**

Neck pain and functional impairment are common complications of traffic accidents (TAs); however, the effects of manual therapy on these symptoms have rarely been studied in the literature. Thus, this randomized controlled trial aims to assess the effectiveness and safety of non-resistance manual therapy (NRT)—a treatment combining mobilization and pressure release techniques—on acute neck pain caused by TA.

**Method::**

This study will use a two-armed, parallel, assessor-blinded randomized controlled trial design and will be conducted in the Daejeon Jaseng Hospital of Korean Medicine in South Korea. One hundred twenty patients will be recruited and randomized into an integrative Korean medicine treatment (IMKT) + NRT group and IMKT group in a 1:1 ratio. The primary outcome is a change in the numeric rating scale for neck pain immediately after treatment on hospital day 5 compared to those at baseline. The secondary outcomes are numeric rating scale for radiating arm pain, visual analogue scale for neck pain and radiating arm pain, cervical active range of motion, neck disability index, Patient Global Impression of Change, Short Form-12 Health Survey, and Posttraumatic Stress Disorder Checklist for DSM-5.

**Discussion::**

The findings of this study on the effectiveness and safety of NRT will be helpful for patients with TA-induced neck pain in clinical practice and will provide evidence for developing relevant healthcare-related policies.

**Trial registration::**

This protocol has been registered at Clinicaltrials.gov (NCT04660175).

## Introduction

1

Traffic accidents (TAs) are a common cause of neck pain, and cervical injury and relevant heterogeneous disorders caused by acceleration and deceleration of vehicles are collectively referred to as the whiplash syndrome.^[1]^ The presence of neck pain episodes is the best predictor of the onset of neck pain in the future, and a study that comprehensively analyzed 47 studies reported that approximately 50% of individuals with TA-related neck pain episodes suffered from neck pain even 1 year after the accident.^[2,3]^ Chronic neck pain can increase medical costs and incur social and financial losses due to disabilities. Some clinical guidelines recommend active exercise, passive joint mobilization, heat, ice and massage, electrotherapy, simple analgesics, and nonsteroidal antiinflammatory drugs for treating acute (≥12 weeks of onset) whiplash associated disorders.^[4]^

In Korea, many patients suffering from whiplash associated disorder seek Korean medicine treatment, although it is not covered by auto insurances. According to auto insurance medical cost statistics, Korean traditional medicine accounts for 48% of all medical costs.^[5]^ In Korean traditional medicine, neck pain is generally treated by acupuncture, electroacupuncture, herbal medicine, Chuna manual therapy, pharmacopuncture, bee-venom pharmacopuncture, cupping therapy, and Doin therapy.^[6]^

Chuna manual therapy is an advanced form of traditional Korean manual therapy that incorporates various forms of manual therapies used in other countries.^[7]^ Cervical nonresistance manual therapy (NRT) is a type of Chuna therapy comprising joint mobilization and pressure release techniques. Mobilization techniques are used in osteopathy and chiropractic therapies. Manual therapy using a pressure release technique is also performed in various countries worldwide.^[8–11]^

Many studies have suggested that compared to treatments for acute whiplash injury that involve joint fixation, treatments that do not involve joint fixation, such as movement within range of motion (ROM) and mobilization, are more effective in the long term.^[4,12–14]^ However, well-designed randomized controlled trials (RCTs) on these manual therapies are lacking. This parallel-group RCT aims to assess the effectiveness and safety of NRT on TA-induced neck pain. The hypothesis is that additional NRT with integrative Korean medicine treatment (IKMT) is superior to IKMT alone.

## Method

2

### Study setting

2.1

This is a protocol for a two-arm parallel RCT that will be conducted in the Daejeon Jaseng Hospital of Korean Medicine. This protocol was approved by the Institutional Review Board at the Daejeon Jaseng Hospital of Korean Medicine prior to patient recruitment (JASENG 2020-10-007). Further, the protocol has been registered at Clinicaltrials.gov (NCT04660175), and the progress of the study will continue to be updated. One hundred twenty inpatients of Daejeon Jaseng Hospital of Korean Medicine with TA-induced acute neck pain who will meet the inclusion criteria and sign an informed consent form will be enrolled. The patients will be recruited within the hospital. Once enrolled, the patients will complete seven visits from hospital day 1 and complete six surveys during their hospital stay and one survey after discharge.

### Participants

2.2

#### Inclusion criteria

2.2.1

1.Age 19 to 70 years2.TA-induced acute neck pain that developed in the last 7 days3.Hospitalization due to acute neck pain4.Numeric rating scale (NRS) of neck pain ≥55.Voluntary signing of a written informed consent form to participate in the clinical trial

#### Exclusion criteria

2.2.2

1.Diagnosis of a severe disease that could cause acute neck pain (e.g., spinal metastasis of tumor, acute fracture, spinal dislocation)2.Progressive neurological defect or severe neurological symptoms3.Pain caused by soft tissue diseases and not the spine (e.g., tumor, fibromyalgia, rheumatoid arthritis, gout)4.Other chronic diseases that may hinder the interpretation of the effects or outcomes of treatment (e.g., stroke, myocardial infarction, kidney diseases, diabetic neuropathy, dementia, epilepsy)5.Current use of steroids, immunesuppressants, antipsychotic drugs, or other drugs that may affect the study outcomes6.Pregnancy, plan to conceive, or breastfeeding7.Cervical surgery or procedure in the past 3 weeks8.Severe mental disorder9.Less than 1 month since participation in another clinical trial, plan to participate in a study within 12 weeks of enrolment, or plan to participate in another clinical trial during the follow-up period10.Failure to sign the consent form to participate in the study11.Other reasons that hinder participation in the clinical trial as determined by the investigators

### Interventions

2.3

The participants will be randomized into the experimental group and control group. The control group will receive acupuncture, Chuna therapy, pharmacopuncture therapy, and herbal medicine treatments during their hospital stay, while the experimental group will receive NRT in addition to IKMT. All interventions will be performed by Korean medicine doctors with at least 1 year of clinical experience who have been trained for the trial and are familiar with the study procedure.

#### Experimental group: IKMT + NRT

2.3.1

For the experimental group, four sessions of NRT will be administered from hospital day 2 to 5, and IKMT will be administered daily. Each session of NRT will last for about 10 minutes.

During the NRT, the patient will be seated, and the therapist will apply pressure to the cervical treatment point while firmly supporting the patient's head and progressively extending the neck to move the joint. The therapist will apply pressure to the posterior neck with the thumb and other fingers while supporting the occipital region with the dorsum of the hand.

With the patient seated on a chair, the therapist will place the thumb and index finger on the areas around the articular pillar in the upper cervical region with tense muscles or on the acupoints GB20, BL10, GB21, or SI15; support the back of the patient's head with the 1^st^ and 2^nd^ metacarpal bone; and place the other hand on the patient's forehead. Then, light flexion and extension will be repeated within the ROM of the cervical spine without pain. The weight of the patient's head will add weight to the hand supporting the head and, thus, will transfer pressure to the thumb and index finger, and compression and relaxation will be repeated based on the transferred pressure. During the treatment, the therapist will comfort the patient by assuring them that the treatment does not cause pain so that the patient can relax the neck muscles. Once the targeted area is adequately flexed and extended over a sufficient period of time, the pressure points will be moved to the central and lower neck to repeat the procedure. The range of cervical extension increases at the lower neck area (Figure S1, Supplemental Digital Content).

#### Control group: IKMT

2.3.2

This group will receive acupuncture, Chuna therapy, pharmacopuncture therapy, and herbal medicine treatments during their hospital stay.

#### Concomitant treatments

2.3.3

The participants will not be prevented from seeking additional treatment for pain during the study period. They will be instructed to notify the investigator immediately they develop an adverse event or receive additional treatment, which will subsequently be recorded in detail.

### Criteria for discontinuing

2.4

1.In the case of participant who have been found to have a disease that could affect the decision of the study result that was not discovered at baseline assessment.2.During the clinical study period, when the participant or participant's legal representative requests to discontinue the study, or the participant withdraws consent.3.Confirmation during treatment.4.Existence of a problem in performing medical or oriental medical treatment for neck pain.5.In case the continuation of participation is not appropriate due to the judgment of the researcher.

### Outcome measures

2.5

#### Primary outcome

2.5.1

##### NRS for neck pain

2.5.1.1

It is a measure of the patient's subjective neck pain. Patients are instructed to choose a number from 0 to 10 that best represents the degree of their current pain (0 for no pain, 10 for the worst imaginable pain).^[15]^

#### Secondary outcomes

2.5.2

##### NRS for radiating arm pain

2.5.2.1

It is a measure of patients’ subjective radiating arm pain. Patients are instructed to choose a number from 0 to 10 that best represents the level of their current discomfort (0 for no pain, 10 for the worst imaginable discomfort).^[15,16]^

##### Visual Analogue Scale for (VAS) neck pain and radiating arm pain

2.5.2.2

The VAS is a 100-mm line with one end indicating no pain and the other end indicating the worst imaginable pain, and patients are instructed to choose a point on the line that indicates their level of pain, which represents their neck pain and radiating arm pain in the past week.^[15,17]^

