### Participant timeline

2.6

At the screening visit, the participants will be enrolled after signing a written consent form, and those who qualify per the inclusion/exclusion criteria will proceed with the trial. The detailed timeline is shown in Table 1.

**Table 1 T1:** Schedule of study.

Time point	Study period						
	Screening	Active treatment				Follow-up	
	Day 1 (visit 1)	Day 2 (visit 2)	Day 3 (visit 3)	Day 4 (visit 4)	Day 5 (visit 5)	Discharge (visit 6)	12 wks (visit 7)
Enrolment							
Eligibility screening	○						
Written informed consent	○						
Sociodemographic hic characteristics	○						
Information about accident	○						
Randomized allocation		○					
Credibility and expectancy questionnaire		○					
Intervention							
IKMT + NRT	Δ (only IKMT)	○	○	○	○	Δ (only IKMT)	
IKMT	○	○	○	○	○	○	
Assessment							
Check symptoms and Med change	○	○	○	○	○	○	○
NRS for neck pain	○	○∗	○∗	○∗	○∗	○	○
VAS for neck pain		○∗	○∗	○∗	○∗	○	
Neck ROM		○∗	○∗	○∗	○∗	○	
NRS for arm pain		○∗	○∗	○∗	○∗	○	○
VAS for arm pain		○∗	○∗	○∗	○∗	○	
NDI		○		○†		○	○
SF-12		○		○†		○	○
PGIC				○†		○	○
PCL-5-K		○		○†		○	○
Adverse events		○	○	○	○	○	○

If Day 5 (visit 5) and day of discharge are the same, then the assessment for Day 5 (visit 5) could be replaced by discharge assessment. The follow-up visit at 12 wks after registration will have a time window of ± 14 days. F/U = follow-up, IKMT = integrative Korean medicine therapy, NDI = neck disability index, NRS = numeric rating scale, NRT = non-resistance technique, PCL-5-K = post-traumatic stress disorder checklist for DSM-5, PGIC = patient global impression of change, ROM = range of motion, SF-12 = 12-item short-form health survey, VAS = visual analogue scale.

∗ Additional evaluation after treatment.

† Investigate only if Day 4 ad 5 (visit 4, 5) and day of discharge are the same.

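### The VAS asks about pain over the past week but is taken before and after each Day 2–5 treatment, so same-day pairs show almost no immediate effect and Day 2–5 change is diluted

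*Protocol article*

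**What the plan says.** Section 2.5.2.2 of the protocol article defines the VAS as a mark on a 100-mm line "which represents their neck pain and radiating arm pain in the past week".

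Table 1 (section 2.6) has the rows "VAS for neck pain" and "VAS for arm pain". Both are ticked on Days 2, 3, 4 and 5, each time with an asterisk that the footnote explains as "Additional evaluation after treatment". Both are ticked once more at discharge, and neither is ticked on Day 1 or at 12 weeks.

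On treatment, section 2.3.1 says "four sessions of NRT will be administered from hospital day 2 to 5" and "Each session of NRT will last for about 10 minutes".

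The neck NRS in section 2.5.1.1 works differently: patients "choose a number from 0 to 10 that best represents the degree of their current pain". The arm NRS in section 2.5.2.1 also asks about the present.

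Section 2.2.1 admits patients with "acute neck pain that developed in the last 7 days". Section 2.11 lists the VAS among the outcomes analysed as change from baseline at each time point, with a time-by-group interaction, and adds areas under the curve during treatment. No section gives another VAS recall period for the in-hospital assessments.

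**The concern.** A rating taken before and after a short session is meant to show what that session did. A question about the past week cannot do that, because the answer is dominated by days that both ratings share. The same difficulty, in weaker form, affects the change across the four treatment days: at Day 5 most of the recalled week lies before the first NRT session.

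The two VAS items are secondary outcomes that sit beside NRS items on the same Day 2–5 schedule. If the NRS moves and the VAS does not, readers may take this as failed corroboration when the recall wording alone could produce it. The areas under the curve during treatment would inherit the same dilution.

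**Working it through.** **The plan's own figure.** The article gives no figure for the VAS. Its only sizing figure is in section 2.7: 41 per group, raised to 60 for 30% withdrawal. With d = 0.63, r = 0.5, two-sided alpha 0.05 and the stated 90% power, the normal approximation for ANCOVA is

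n = 2(1.960 + 1.282)² × (1 − 0.5²) / 0.63² = 39.7, so 40 per group.

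The exact t calculation gives 41, and 41/0.7 = 58.6, so 59, close to the stated 60. The figure reproduces and plays no part in what follows.

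**Inputs.**
- Recall window: 7 days (section 2.5.2.2).
- Session length: about 10 minutes (section 2.3.1).
- First NRT session on Day 2, so Day 5 is 3 days later (section 2.3.1, Table 1).
- VAS baseline: the Day 2 pre-treatment rating, the first VAS in Table 1.
- Assumed: the patient's mark is the even average of pain over the 7 days. The article does not say how the week is to be summarised.
- Assumed: ratings within a day are 10 minutes to 1 hour apart. The article gives no interval.

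**Overlap of two windows L days apart:** 1 − L/7.

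**Share of a benefit that appears L days after it begins:** L/7 if it is immediate and lasting. If it builds linearly from zero, the share of the level reached by then is 0.5 × L/7.

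| Interval between ratings | L (days) | Overlap | Immediate benefit shown | Linear benefit shown |
|---|---|---|---|---|
| 10 minutes, same day | 0.0069 | 99.9% | 0.1% | – |
| 1 hour, same day | 0.0417 | 99.4% | 0.6% | – |
| Day 2 to Day 3 | 1 | 86% | 14% | 7% |
| Day 2 to Day 4 | 2 | 71% | 29% | 14% |
| Day 2 to Day 5 | 3 | 57% | 43% | 21% |

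The last row is 3/7 = 0.43 and 0.5 × 3/7 = 0.21.

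**Days before the accident.** If onset was k days before Day 1, then k + 1 days have passed by Day 2, and 7 − (k + 1) = 6 − k days of the window precede onset. With k = 2, for illustration, that is 4 of the 7 days. Entry requires only that onset be recent, so this can be common. It blurs the VAS baseline in both groups alike.

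**The case against.** The strongest reply is that little hangs on this. The VAS is secondary. The NRS already records neck and arm pain as they are now, on the same before-and-after schedule, so the immediate effect is covered. The recall problem applies to both groups, so it dilutes a difference and does not create one. The article states both recall periods openly, so an attentive reader could explain a discordant result. All of this stands, and it limits the weight of the point. It does not remove the conflict between section 2.5.2.2 and Table 1.

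Three stronger readings are tempting, and the article does not support them.

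- *The VAS cannot register any change in the treatment phase.* This fits only the same-day pairs. By Day 5 part of a benefit shows, and the discharge rating shows more as the stay lengthens, although Table 1 allows discharge to fall on Day 5.
- *3/7 is an upper limit.* It follows only from even weighting. Patients who give recent days more weight, or who rate only the time since the accident, would show more than 43%. Patients who report their worst pain could show less.
- *Power for the VAS collapses.* Shrinking 0.63 SD to 0.27 or 0.135 SD, with 42 per group and r still 0.5, gives 29% or 11%. But averaging over a week also lowers the SD, and overlapping windows raise the baseline correlation. Suppose momentary pain correlates 0.5 over 3 days with exponential decay, and there is no added recall noise. The weekly SD is then 0.79 of the momentary SD, the correlation is 0.82, and power is about 78% or 28%. The answer depends on the model, and section 2.7 does not tie 0.63 or 0.5 to the VAS. No power figure should be quoted.

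**Conclusion.** The point holds as a mismatch between the VAS recall period and its schedule. For the same-day pairs it is nearly complete: the windows overlap by more than 99%, so a patient who answers as instructed can show essentially no immediate effect. For Day 2 to Day 5 the measure is strongly diluted but not blind: about 43% of an immediate lasting benefit, or about 21% of a linear one, under even averaging over the week. Those two percentages depend wholly on that assumption; the overlap of the windows does not.

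If patients in practice answer by current pain, the dilution shrinks. The score is then no longer the variable that section 2.5.2.2 defines, and patients may differ in how they answer. The primary NRS outcome and the sample size are untouched. This is worth correcting because the correction is cheap, but it does not threaten the trial's main conclusion.

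**What to change.** Ask for current pain on the neck and arm VAS at every assessment from Day 2 to discharge, in section 2.5.2.2 and on the case report form. This is one line in each place and adds no visits. The downside is that the VAS then largely duplicates the NRS and past-week pain is no longer recorded.

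If past-week pain is wanted, keep the wording, drop the same-day post-treatment VAS from Table 1, and state that the Day 2–5 VAS is not read as a measure of immediate response. This costs no new data collection, but it leaves the NRS as the only pain scale for the immediate effect.

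If ratings have already been collected, report which wording patients actually saw and interpret the VAS accordingly.

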##### Cervical spine active ROM

2.5.2.3

The maximum active ROM for the cervical spine (flexion, extension, lateral flexion to the left and right, rotation to the left and right) without pain are measured.

##### Neck Disability Index (NDI)

2.5.2.4

Functional status will be assessed using the NDI. The NDI was developed as an index for the severity of neck disability. The NDI comprises 10 items, and each item is scored on a scale from 0 to 5. The total possible score is 50. The total score is divided by the number of answered items to compute the average score.^[17,18]^

##### Patient Global Impression of Change (PGIC)

2.5.2.5

The PGIC allows patients to subjectively assess the level of their improvement on a seven-point scale as follows: 1, very much improved; 2, much improved; 3, minimally improved; 4, no change; 5, minimally worse; 6, much worse; or 7, very much worse.^[19]^

##### Short Form-12 Health Survey version 2 (SF-12 v2)

2.5.2.6

The SF-12 is a questionnaire for health-related quality of life (HRQoL), and it comprises 12 items in 8 domains (physical functioning, role- physical, bodily pain, general health, vitality, social functioning, role-emotional, and mental health). The questionnaire is completed in about 5 minutes, and a higher score indicates a better HRQoL. The SF-12 is used to assess functional health and well-being of patients and healthy individuals. The Korean version of the SF-12 was validated by Kim et al based on 1000 Korean people for assessing HRQoL.^[20]^

##### The Posttraumatic Stress Disorder Checklist for DSM-5 (PCL-5-K)

2.5.2.7

The PCL is one of the most widely used self-reported scales for post-traumatic stress disorder. For patients involved in a TA, it is used to assess the level of post-traumatic stress disorder caused by trauma from TAs. We will use the Korean version of the PCL that has been adapted and validated by Kim et al.^[21]^

#### Drug consumption

2.5.3

The types and doses of drugs taken during the study period (drugs prescribed for current illness or rescue drugs) will be examined based on the questionnaires. The patients will also be instructed to record the frequency of other treatments, such as physiotherapy and injections.

#### Adverse events (AEs)

2.5.4

AEs refer to undesirable and unintended signs, symptoms, or diseases that occur post-procedurally during the clinical trial (e.g., laboratory abnormalities), and they do not have to be causatively associated with the procedure. The investigators will assess the causality between the treatment modality and each AE based on the 6-level World Health Organization-Uppsala monitoring center causality assessment system (1 = definitely related, 2 = probably related, 3 = possibly related, 4 = probably not related, 5 = definitely not related, and 6 = unknown). In addition, all AEs will be categorized into three severity levels based on the Spilker classification system (Mild (1): does not significantly impair daily activities (function) nor require additional medical intervention; Moderate (2): significantly impairs daily activities (function) and may require additional medical intervention but will resolve; Severe (3): severe AE that requires intense medical intervention and leaves sequela).^[22]^

### Participant timeline

2.6

At the screening visit, the participants will be enrolled after signing a written consent form, and those who qualify per the inclusion/exclusion criteria will proceed with the trial. The detailed timeline is shown in Table 1.

**Table 1 T1:** Schedule of study.

Time point	Study period						
	Screening	Active treatment				Follow-up	
	Day 1 (visit 1)	Day 2 (visit 2)	Day 3 (visit 3)	Day 4 (visit 4)	Day 5 (visit 5)	Discharge (visit 6)	12 wks (visit 7)
Enrolment							
Eligibility screening	○						
Written informed consent	○						
Sociodemographic hic characteristics	○						
Information about accident	○						
Randomized allocation		○					
Credibility and expectancy questionnaire		○					
Intervention							
IKMT + NRT	Δ (only IKMT)	○	○	○	○	Δ (only IKMT)	
IKMT	○	○	○	○	○	○	
Assessment							
Check symptoms and Med change	○	○	○	○	○	○	○
NRS for neck pain	○	○∗	○∗	○∗	○∗	○	○
VAS for neck pain		○∗	○∗	○∗	○∗	○	
Neck ROM		○∗	○∗	○∗	○∗	○	
NRS for arm pain		○∗	○∗	○∗	○∗	○	○
VAS for arm pain		○∗	○∗	○∗	○∗	○	
NDI		○		○†		○	○
SF-12		○		○†		○	○
PGIC				○†		○	○
PCL-5-K		○		○†		○	○
Adverse events		○	○	○	○	○	○

If Day 5 (visit 5) and day of discharge are the same, then the assessment for Day 5 (visit 5) could be replaced by discharge assessment. The follow-up visit at 12 wks after registration will have a time window of ± 14 days. F/U = follow-up, IKMT = integrative Korean medicine therapy, NDI = neck disability index, NRS = numeric rating scale, NRT = non-resistance technique, PCL-5-K = post-traumatic stress disorder checklist for DSM-5, PGIC = patient global impression of change, ROM = range of motion, SF-12 = 12-item short-form health survey, VAS = visual analogue scale.

∗ Additional evaluation after treatment.

† Investigate only if Day 4 ad 5 (visit 4, 5) and day of discharge are the same.

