### Allocation and concealment

2.8

The same number of patients will be assigned to each groups using a randomization table generated by a statistician that is not directly involved in the study. Block randomization will be used, and the size of each block will be randomly set to 2, 4, or 6. The assignment results will be sealed in an envelope and stored in a double-locked safe until immediately before the initiation of the treatment for the participants who sign the consent form. After opening the envelope, no one can alter the assignment results, and the random number displayed inside the envelope will be assigned to the patient and recorded in the electronic medical records. Only investigators registered for the trial can screen, enroll, and assign a random envelope to the participants.

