### Blinding (masking)

2.9

Due to the nature of the intervention, it will be impossible to blind the participants and the physician, so we will blind the assessor, who is not involved in the screening or intervention, during the outcome measurements.

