### Statistical methods

2.11

In this study, both the intention-to-treat and per-protocol analyses will be performed, with intention-to-treat as the primary analysis. In the per-protocol analysis, participants who receive at least three sessions of treatment will be analyzed separately. The NRT + IKMT group and IKMT group will be compared, and the aim is to evaluate the superiority of NRT + IKMT.

Missing values will be processed through a mixed model for repeated measures in the primary analysis, and multiple imputations and the last observation carried forward will be performed for sensitivity analysis. For the Kaplan-Meier curve and log-rank test, the patients who drop out will be right censored, and regarding intermittent censoring, we will assume that no event occurred during the specified time period.

The sociodemographic characteristics of the participants and treatment expectancy will be evaluated by group. Continuous variables will be presented as mean (standard deviation) or median (quartile), and the two groups will be compared using the Student *t* test or Wilcoxon-rank sum test depending on the distribution pattern. Categorical variables will be presented as frequency (%) and will be analyzed using chi-square test or Fisher's exact test.

The endpoints of this clinical trial are the changes in the continuous outcomes (NRS, VAS, NDI, SF-12, ROM, PCL-5-K) at each time point from the baseline. A linear mixed model will be used as the primary analysis, and a random intercept model, which includes subject the random effects. Fixed effects will include baseline outcomes and clinically important covariant factors that are statistically significantly differ between groups at baseline as the covariates. In addition, time, group allocation, and the time and group interaction will be included in the model to examine the differences in the amount of change over time between the groups. For sensitivity analysis, we will perform analysis of covariance on the multiple imputations and last observation carried forward sets with the same covariates as those in the primary analysis and the group set as the fixed factor.

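### The covariate rule does not bar an expectancy score taken after open allocation, so the primary and sensitivity models can adjust for a variable that allocation itself has shifted

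*Protocol article*

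**What the plan says.** **Timing.** In the protocol article, Participant timeline (2.6), Table 1 marks the "Credibility and expectancy questionnaire" on Day 2 only. "Randomized allocation" is marked on the same day, and so is the first NRT session. Under Allocation and concealment (2.8) the assignment is "stored in a double-locked safe until immediately before the initiation of the treatment for the participants who sign the consent form". Unsealing, questionnaire and first session therefore share one visit, and the article does not say in which order the first two occur.

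**Blinding.** Section 2.9 states that "it will be impossible to blind the participants and the physician".

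**Analysis.** Statistical methods (2.11) says "The sociodemographic characteristics of the participants and treatment expectancy will be evaluated by group", and for continuous variables that "the two groups will be compared using the Student *t* test or Wilcoxon-rank sum test depending on the distribution pattern". For the primary linear mixed model, the fixed effects include the baseline outcome and "clinically important covariant factors that are statistically significantly differ between groups at baseline as the covariates". The sensitivity ANCOVAs on the multiple-imputation and last-observation-carried-forward sets are run "with the same covariates as those in the primary analysis".

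**The concern.** For a variable measured before allocation, a between-arm significance test can pick up only chance imbalance, about 5% of the time for each variable. An expectancy score taken after the patient knows the arm is different. In an open add-on design the patient then knows whether something extra is coming, so a between-arm difference may be a consequence of allocation. The test would detect that consequence, and the covariate rule could then enter it in the primary model.

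Adjusting for such a variable changes the question. The contrast is no longer the total effect of adding NRT to IKMT but an effect conditional on a post-randomisation variable, without the protection of randomisation. Because the sensitivity analyses carry the same covariates, they would repeat the adjustment and could not expose it.

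**Working it through.** **Plan's own figures (2.7).** Inputs: Cohen's d = 0.63, baseline–endpoint correlation r = 0.5, two-sided alpha 0.05, power 90%.

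- ANCOVA, normal approximation: n = 2(1 − r²)(z₀.₉₇₅ + z₀.₉₀)²/d² = 39.7, so 40 per arm. The noncentral-t version gives 41, as stated.
- Inflation for 30% withdrawal: 41/0.7 = 58.6, so 59 against the stated 60. Sixty enrolled leaves 60 × 0.7 = 42 evaluable.
- Power of the ANCOVA without expectancy: 91% at 42 per arm, 98% at 60.

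These figures are not in dispute here. (The same section also gives beta as 0.2, which is a separate matter.)

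**Assumptions not in the documents.** Known allocation shifts expectancy by a SD. Within arm, expectancy has correlation b with the outcome and is unrelated to the baseline score. The total effect stays at 0.63. Central case a = 0.5, b = 0.3; range a = 0.3 to 0.8, b = 0.2 to 0.4. The calculation uses an ANCOVA at one time point as a stand-in for the mixed model, and takes expectancy to be judged clinically important.

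**Step 1: how often the test selects expectancy.** This is the power of a two-sample t test for a shift of 0.5 SD: about 61–62% at 42 per arm and about 77–78% at 60.

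**Step 2: the estimate when expectancy is in the model.** 0.63 − a·b = 0.63 − 0.5 × 0.3 = 0.48 SD.

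**Step 3: the mean estimate under the select-then-adjust rule.** This is 0.63 − b × E[D; selected], where D is the observed between-arm difference in expectancy, counted as zero in trials where expectancy is not selected. D has mean 0.5 and standard error √(2/n).

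- n = 42: SE = 0.218, cut-off about 0.434, P(selected) = 0.62. E[D; selected] = 0.5 × 0.62 + 0.218 × 0.381 = 0.39. Mean estimate 0.63 − 0.3 × 0.39 = 0.51.
- n = 60: SE = 0.183, cut-off about 0.362, P(selected) = 0.78. E[D; selected] = 0.5 × 0.78 + 0.183 × 0.299 = 0.44. Mean estimate 0.63 − 0.3 × 0.44 = 0.50.

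**Step 4: power under the rule, by simulation.** In each simulated trial expectancy entered the ANCOVA only if its t test gave p < .05.

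| Evaluable per arm | Selected | Mean estimate (SD) | Power without expectancy | Power under the rule |
|---|---|---|---|---|
| 42 | 61–62% | 0.51 | 91% | 76–77% |
| 60 | 77–78% | 0.50 | 98% | 88–89% |

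**Step 5: range, at 41 per arm.**

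| Shift a (b = 0.2 to 0.4) | Selected | Mean estimate (SD) | Power |
|---|---|---|---|
| 0 | about 5% | 0.63 | about 90% |
| 0.3 | 26–28% | 0.60 to 0.57 | 86 to 85% |
| 0.5 | 61% | 0.55 to 0.47 | 80 to 71% |
| 0.8 | 94–95% | 0.48 to 0.31 | 64 to 39% |

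The row a = 0 is the case of a score completed before the envelope is opened: no systematic bias.

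**The case against.** Five points can be made for the plan.

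1. **Expectancy is not named as a covariate.** A factor must be clinically important as well as significantly different at baseline, and nothing calls expectancy clinically important. This stands: the rule may admit expectancy, and it would be wrong to say that it must.

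2. **Harm needs two readings at once.** A score taken before unsealing gives only chance imbalance. A score taken after it is not a baseline factor, so the rule read literally leaves it out. This has force, but the article does not secure the literal reading. Expectancy is compared alongside sociodemographic characteristics. Table 1 also takes VAS, ROM, NDI, SF-12, PCL-5-K and arm-pain NRS for the first time on Day 2, so a Day 2 score could easily pass as baseline.

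3. **Row order in Table 1 is no evidence of sequence.** A reader might infer from the questionnaire's place below allocation that it is completed afterwards. The documents do not support that. Rows are grouped by type, and the Day 2 outcome readings stand below the intervention rows although a further reading after treatment is marked separately. The order is simply not fixed.

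4. **Order within a visit is a matter for the full protocol or SOP.** Agreed. Silence on the order is not itself the fault. The fault is a stated analysis rule that gives no protection if the order goes the wrong way.

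5. **A score taken after allocation is legitimate as a description** of belief in the assigned treatment in an open trial. Agreed; reporting it by group is fine.

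A reader might also put the loss of power at 91% to 71%, which is the power at 0.48 SD with 42 per arm. That assumes adjustment in every trial, whereas expectancy is selected in only about 61–62% of trials of that size.

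**Conclusion.** The point holds in conditional form. As written, the covariate rule can admit to the primary model, and to the sensitivity ANCOVAs, an expectancy score that open allocation has shifted. This requires that the score be taken after the arm is known and be treated as a clinically important baseline factor. The article neither states nor excludes either condition.

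Under those conditions, and with an assumed 0.5 SD shift and correlation of 0.3, the primary estimate loses on average 0.12 to 0.13 SD of 0.63, about a fifth. Over the assumed range the mean estimate runs from about 0.60 down to 0.31 SD. The direction, towards no effect, assumes that knowing one will receive NRT raises expectancy and that higher expectancy goes with more pain relief. These sizes illustrate what the rule allows; they do not predict what will happen in this trial. The change is worth making because it closes the gap at almost no cost.

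**What to change.** In Statistical methods (2.11), replace the significance-based rule by a pre-specified list of covariates, all measured before allocation, for both the primary mixed model and the sensitivity ANCOVAs. Add that any credibility or expectancy score obtained after allocation is reported by group descriptively and enters neither model.

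The questionnaire need not be moved for this. If expectancy is wanted as a covariate or effect modifier, state in the schedule or SOP that it is completed before the envelope is opened, on Day 1 or on Day 2 before allocation.

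Cost: one or two sentences in the analysis section and, for the second option, one line on order within the visit. Sample size is unaffected. The small downside of a score taken before allocation is that it reflects expectations of the treatments in general and does not describe belief in the assigned arm.
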